### Trial Interventions

2.7

All patients receive routine standardized neurocritical care management, including airway management, temperature regulation, blood pressure control, electrolyte balance maintenance, infection control, nutritional support, etc. Additionally, all patients undergo passive range of motion therapy and ergometer cycling therapy daily, administered by a physiatrist blinded to the group allocation.

All patients receive EA or sham‐EA treatment in the supine position at 9 am for 30 min once a day for 14 consecutive days (Figure 2). One certified acupuncturist performs EA and sham‐EA treatments for patients in both groups. Disposable sterile acupuncture needles (0.25×25 mm, Hanyi brand, Changchun AIK Medical Devices Co., China) and EA apparatuses (SDZ‐V, Hwato Brand, Suzhou Medical Appliance Factory, China) are used in both groups.

**FIGURE 2 brb370637-fig-0002:**
[figure not shown]
Electroacupuncture and sham‐electroacupuncture treatments. EA, electroacupuncture.

Patients in the EA group receive acupuncture at Shuigou (also known as Renzhong, GV26, DU 26) and Yintang (updated number GV24+, previous number GV29). Shuigou is located on the midline above the upper lip, at the junction of the upper one‐third and lower two‐thirds of the philtrum midline (Institute of Acupuncture and Moxibustion, China Academy of Chinese Medical Sciences 2021). Yintang is located on the forehead, at the midpoint between the two medial ends of the eyebrow (Institute of Acupuncture and Moxibustion, China Academy of Chinese Medical Sciences 2021). After the skin is sterilized, sterile adhesive pads are placed in the area between the nose and upper lip and in the area between the eyebrows. Acupuncture needles are inserted through the adhesive pads approximately 10–15 mm into the skin. The acupuncture needle is inserted obliquely (30°–45°) upward to the direction of the nose for Shuigou and is inserted obliquely (15°–30°) downward to the direction of the nose for Yintang. Paired electrodes from the EA apparatus are clipped to the needle handles at Shuigou and Yintang. The EA stimulation lasts for 30 min with a wave of rarefaction and condensation (4 Hz/20 Hz) and a current intensity of the maximum withstand current within 10 mA. The maximum withstand current is defined as the maximum current intensity that does not cause any discomfort with a Nociception Coma Scale‐Revised score (Chatelle et al. 2012) above 4 and is different from the baseline value.

Patients in the sham‐EA group receive sham‐EA at sham‐Shuigou (1 cun [≈20 mm] lateral to Shuigou) and sham‐Yintang (1 cun [≈20 mm] lateral to Yintang). After the skin is sterilized, sterile adhesive pads are placed in the area between the nose and upper lip and in the area between the eyebrows. Acupuncture needles are inserted into the adhesive pads but do not pierce the skin. Paired electrodes from the EA apparatus via sham connecting cords are clipped to the needle handles at sham‐Shuigou and sham‐Yintang. The sham connecting cords are similar in appearance to the normal ones, but the inner wires in the sham connecting cords are cut off and cannot conduct electricity. The sham‐EA stimulation lasts for 30 min with a wave of rarefaction and condensation (4 Hz/20 Hz) and a current intensity of the maximum withstand current within 10 mA.

### Study Procedures

2.8

At the time point of screening, demographics, education, time from injury, injury location, right‐ or left‐handed, medical history, current medications, CRS‐R score, and state of DOC are recorded (Table 1). After the enrollment, the following neurophysiological and neuroimaging examinations are performed before the first EA or sham‐EA treatment: EEG, somatosensory evoked potential (SEP), brainstem auditory evoked potential (BEAP), resting‐state functional MRI (rs‐fMRI), amide proton transfer (APT) imaging, intravoxel incoherent motion (IVIM) imaging, neurite orientation dispersion and density imaging (NODDI), and BCI. During the 14 days of treatment, the CRS‐R score is assessed every day after the treatment. After the last EA or sham‐EA treatment, the CRS‐R score and the above‐mentioned neurophysiological and neuroimaging examinations are performed again. During hospitalization, vital signs and adverse events (AEs) are monitored, and concomitant treatments are documented. Glasgow Outcome Scale‐Extended (GOS‐E) score at 30 and 90 days after randomization are collected.

**TABLE 1 brb370637-tbl-0001:** Timing and content of the study assessments.

Items	Day of enrollment					
	Screening	Pre‐treatment assessments	14‐day treatment	Post‐treatment assessments	Follow up	
					30 days	90 days
Written informed consent	●					
Inclusion and exclusion criteria	●					
Demographics	●					
Education	●					
Time from injury	●					
Brain injury location	●					
Right‐ or left‐handed	●					
Medical history	●					
Current medication	●					
Physical examination	●					
CRS‐R score	●		●	●		
State of consciousness	●		●	●		
Brain–computer interface assessment		●		●		
EEG, SEP, BAEP		●		●		
rs‐fMRI, APT, IVIM, NODDI		●		●		
GOS‐E					●	●
Vital signs monitoring	●	●	●	●		
Adverse events			●	●		
Concomitant therapies	●					

Abbreviations: APT, amide proton transfer; BAEP, brainstem auditory evoked potential; CRS‐R, Coma Recovery Scale‐Revised; EEG, electroencephalogram; GOS‐E, Glasgow Outcome Scale‐Extended; IVIM, intravoxel incoherent motion; NODDI, neurite orientation dispersion and density imaging; rs‐fMRI, resting‐state functional MRI; SEP, somatosensory evoked potential.

### Assessment of the Level of Consciousness

2.9

The level of consciousness is assessed using CRS‐R scores and a BCI system (Figure 3), which is conducted by trained researchers who are blinded to the grouping results. The CRS‐R has a maximum score of 23 points (higher scores indicate higher levels of consciousness) and consists of 23 items broken into 6 subscales: auditory, visual, motor, verbal, communication, and arousal functions. The Chinese version of CRS‐R is used in this study (Di et al. 2017; Zhang et al. 2019). All patients receive three CRS‐R assessments administered at 24‐h intervals​​ during both pre‐treatment screening and post‐treatment evaluation. Diagnoses of UWS, MCS (including MCS‐ and MCS+), and emergence from the minimally conscious state (EMCS) are based on at least two CRS‐R assessments (Bruno et al. 2011; Giacino et al. 2002), with the higher score designated as the baseline and outcome CRS‐R score for each patient. Additionally, daily CRS‐R assessments are conducted throughout the 14‐day treatment period.

**FIGURE 3 brb370637-fig-0003:**
[figure not shown]
Brain–computer interface assessment system. SSVEP, steady‐state visually evoked potential; SVM, support vector machine.

Our previously published EEG‐based BCI system is also used to assess the level of consciousness by analyzing P300 and steady‐state visual evoked potentials (SSVEP) when participants perform cognitive tasks (Pan et al. 2020). Briefly, participants are asked to focus on a photo of themselves or a randomly selected stranger and count the flashes of the photo's frame according to audiovisual instructions. The photograph‐related P300 and SSVEP are detected and analyzed. A total of 50 trials are given to each patient. BCI accuracy is calculated as the ratio of the number of trial successes to the total number of trials and is considered a parameter related to the level of consciousness.

### Neurophysiological Assessments

2.10

All patients receive two times of video‐EEG monitoring. The first EEG recording starts 20 min before the first EA or sham‐EA treatment and continues until 24 h after the treatment. The second EEG recording starts 20 min before the last EA or sham‐EA treatment and continues until 24 h after the treatment. EEG signals are collected through 19‐channel monopolar leads with Ag/AgCl cup electrodes (NicoletOne EEG System, USA), placed according to the international 10–20 system. The sampling frequency is 500 Hz and the electrode–skin impedance is lower than 5 kΩ.

All patients receive SEP and BAEP assessments before and after the 14‐day EA or sham‐EA treatment (Nicolet Monitor UltraPro S100, US). All SEPs and BAEPs are assessed for reproducibility and analyzed by one certified neurophysiologist. For SEP, monophasic rectangular‐wave 200 µs stimulus pulses are given to the median nerve, and the intensity is adjusted to produce a visible thumb twitch. A minimum of 500 stimulations are averaged per recording. For BAEP, monoaural click stimuli of 50 µs duration are delivered through shielded headphones at a frequency of 10 Hz and an intensity of 70–90 dB HL. Both ears are stimulated separately. The contralateral ear is masked by 20 dB noise. Three trials of 1,000 clicks are recorded to assess reproducibility.

### Neuroimaging Assessments

2.11

All patients receive two sets of neuroimaging examinations: one is before EA or sham‐EA treatment, and the other is after all the treatments. One set of neuroimaging examinations includes rs‐fMRI, APT, IVIM, and NODDI. MRI data are acquired using a 3T magnetic resonance unit (Philips Ingenia) with a 16‐element phased‐array head coil (Table 2). Resting‐state fMRI is used to examine intrinsic brain networks associated with consciousness by measuring spontaneous low‐frequency fluctuations in the blood oxygen level‐dependent signals. APT is a molecular MRI technique based on chemical exchange saturation transfer that measures the amide proton content, indirectly reflecting the protein content and pH value of a substance. IVIM uses multiple low b values to uncouple restricted diffusion from the pseudo‐diffusion effect of water movement in the capillary bed and can be used to non‐invasively quantify microperfusion. NODDI is an advanced non‐Gaussian diffusion model that can quantitatively estimate specific microstructural changes in terms of neurite density and orientation distribution of axons and dendrites.

**TABLE 2 brb370637-tbl-0002:** Behavioral, neurophysiological, and neuroimaging evaluations.

Items	Time consumed	Aim	Key parameters
Behavioral			
CRS‐R	20 min	Evaluate the neurobehavioral performance	Auditory, visual, motor, verbal, communication, arousal scale
BCI	20 min	Assess the severity of DOC	Accuracy
Neurophysiological			
EEG	24 h	Monitor electrical activity in the brain	Power, ABCD pattern, connectivity, sleep EEG pattern
SEP	30 min	Evaluate the integrity of the sensory pathway	Amplitude, latency
BAEP		Evaluate the integrity of the auditory pathways	Amplitude, latency
Neuroimaging			
rs‐fMRI	45 min	Examine spontaneous brain function by using blood oxygen level–dependent contrast	Amplitude of low‐frequency fluctuations, networks, connectivity
APT		Reflect the protein metabolism in specific brain areas	Magnetization transfer ratio asymmetry
IVIM		Reflect the microcirculation perfusion in specific brain areas	Perfusion fraction, molecular diffusion coefficient, pseudo‐diffusion coefficient
NODDI		Assess the microstructural complexity of neuronal axons and dendrites	Neurite density index, orientation dispersion index, isotropic volume fraction

Abbreviations: APT, amide proton transfer; BAEP, brainstem auditory evoked potential; BCI, brain–computer interface; CRS‐R, Coma Recovery Scale‐Revised; EEG, electroencephalogram; IVIM, intravoxel incoherent motion; NODDI, neurite orientation dispersion and density imaging; rs‐fMRI, resting‐state functional MRI; SEP, somatosensory evoked potential.

3D T1‐weighted images (170 transversal slices, repetition time = 2100 ms, voxel size = 1.0 × 1.0 × 1.0 mm^3^, flip angle = 8°, field of view = 250 × 199 × 170 mm^3^) are acquired before rs‐fMRI (EPI, gradient echo, volumes = 300, repetition time = 2000 ms, echo time = 30 ms, flip angle = 78°, voxel size = 3 × 3 × 3 mm^3^, field of view = 192 × 192 mm^2^, 32 transversal slices). DOC patients should be awake during the fMRI examination, and an arousal facilitation protocol (from the CRS‐R score) should be used if the patient exhibits sustained eyelid closure before the examination. Healthy subjects are instructed to keep their eyes open and to be in a relaxed state during the MRI data acquisition.

APT images are acquired using the 3D TSE‐Dixon approach with a continuous saturation duration of 2 s and an RF saturation amplitude of 2 µT. Saturation frequency offsets were implemented at 3.5, 3.5 ± 0.8, −3.5, −3.5 ± 0.8, and −1560 ppm. At 3.5 ppm, three Z‐spectral images are acquired using a different echo time shift on the order of 0.5 ms. This allows calculating a B0 field map directly based on mDIXON algorithms and then for z‐spectrum correction on a voxel‐by‐voxel basis. The far‐off resonant frequency (−1560 ppm) is acquired for signal normalization. Other imaging parameters were as follows: repetition time /echo time = 6306/7.8; field of view = 210 mm; slice thickness = 6 mm; sensitivity encoding factor = 2. Acquisition time is 11 min 27 s.

IVIM is performed with a short multiple *b* value diffusion‐weighted MRI sequence, using a monopolar pulsed gradient scheme and a spin‐echo‐planar imaging readout, with the following acquisition measures: 10 *b* values (0, 10, 20, 50, 100, 150, 200, 500, 800, 1000 s/mm^2^) in 3 orthogonal directions, repetition time = 7317 ms, echo time = 83 ms, field of view = 210 × 210 mm^2^, slice thickness = 2 mm, acquisition matrix = 104 × 102, in‐plane physical resolution = 2.0 ×2.0 mm^2^, parallel imaging accelerating factor 2.1, 65.3% Fourier encoding. Acquisition time is 4 min and 45 s.

For the NODDI diffusion scan, the field of view is 232 mm in *X* and *Y* and 162 mm in the *Z* direction, with 2.0 mm isotropic voxels. The echo and repetition times were 105 and 5076 ms respectively. Data consist of 127 volumes with 13 non‐diffusion‐weighted images (*b* = 0 s/mm^2^), and 114 diffusion‐encoding gradient directions (6*b* = 500, 48*b* = 1000, and 60*b* = 2000 s/mm^2^), evenly spread over the entire spherical shells using an electrostatic repulsion model, and interspersed in time to minimize gradient heating. Acquisition time is 10 min and 56 s.

### Sample Size

2.12

No prior studies have examined the efficacy of EA in patients with DOC. Therefore, the sample size calculation was based on a clinical trial of transcranial direct current stimulation (tDCS) evaluating its effect on consciousness recovery in DOC patients (Barra et al. 2022). In that study, the total change in the CRS‐R score after sham treatment was −0.1 (±1.6) from baseline, while the total change after tDCS treatment was 1 (±2.6). For this study, we assumed that the sham‐EA group would show a total change in the CRS‐R score of 0 (±1.6), and that EA treatment would result in a 1.3‐point improvement in the CRS‐R score. Using a two‐sided significance test with a 5% type I error, we calculated a minimum of 24 participants per group. To account for a 4% non‐adherence to the treatment protocol and loss to follow‐up, the sample size is set at 50 (25 per group). There is no limitation on the sample size for subgroup stratification.

### Statistical and Analytical Plan

2.13

Under the Intention To Treat principle, all patients who are randomized are included in the analysis of the original allocation group. Baseline and demographic characteristics such as gender, age, time from injury, brain injury location, closed or open TBI, right‐ or left‐handed, GCS score, CRS‐R score, APACHE2 score, etc., will be pooled by treatment group to assess comparability of treatment groups. The primary outcome of the change in CRS‐R score after 14‐day treatment, secondary outcomes of BCI accuracy after 14‐day treatment and the GOS‐E score at 30 days and 90 days will be analyzed using Student's t‐test or Mann‐Whitney U test (whichever is proper) and will be analyzed by bootstrap analyses in general linear models to estimate adjusted odds ratios and associated 95% confidential intervals (adjusted for age, sex, time from injury to enrollment, and baseline CRS score). Two‐sided p values ≤ 0.05 will be considered significant. The pairwise deletion method is used to handle missing data. Statistical analysis will be performed with SPSS version 22 software (SPSS Inc., Chicago, IL, USA).

EEG data are analyzed using MATLAB 2016b (Mathworks, Sherborn, Massachusetts, USA). The immediate effects of EA are explored by analyzing the mean EEG power, pattern, and connectivity at 10 min before the allocated treatment and at four time points after the allocated treatment (10 min, 60 min, 6 h, and 24 h). The prolonged effects of EA are explored by analyzing changes in EEG power, pattern, and connectivity before and after the 14‐day intervention. For each electrode, the mean power values of 5 s epochs are estimated in different standard EEG frequency bands: delta (0.5–4 Hz), theta (4–8 Hz), alpha (8–13 Hz), and beta (13–30 Hz). EEG patterns are determined based on the EEG power spectrum and classified into four categories according to the “ABCD” model, which decodes the integrity of thalamocortical circuitry and the preservation of consciousness (Alkhachroum et al. 2020; Edlow et al. 2021). Functional connectivity is estimated using phase‐synchronization measures. Sleep EEG is rated using the modified Valente's Grade (Yang et al. 2020). For SEP data, the average of N20–P25 peak‐peak amplitude from the right and left sides is calculated. For BAEP, wave IV–V peak‐to‐peak amplitude, wave V latency in ms, and interpeak latency difference (IPL) III–V are selected as main variables.

The preprocessing of fMRI data is conducted using MELODIC in the FMRIB Software Library. The preprocessing pipeline includes removal of the first five volumes to allow signal stabilization, motion correction using MCFLIRT, brain extraction via BET, spatial smoothing with a 5 mm full‐width‐at‐half‐maximum Gaussian kernel, rigid‐body registration, high‐pass filtering with a cutoff of 100 s to remove low‐frequency drifts, and single‐session independent component analysis with automatic dimensionality estimation, and removal of noise components and lesion‐driven artifacts using FIX. The changes in the amplitude of low‐frequency fluctuations of the region of interest are analyzed. Seed‐based correlation analysis is performed with DPARSF‐A using a 6 mm radius sphere for each node of the seven networks: higher‐order networks (the default mode network, dorsal attention network, executive control network, and salience network) and sensory‐related lower‐order networks including the visual network, sensory input auditory network, and sensorimotor network. Group‐level analyses are performed using Statistical NonParametric Mapping (http://www.nisox.org/Software/SnPM13/) for each network. The APT imaging analysis is performed using the IntelliSpace Portal v.8.0.1 (Philips Healthcare). The quantitative APT analysis is performed in selected ROIs, which include cortex (frontal, parietal, temporal cortex, occipital), periventricular white matter, thalamus, basal ganglia, insular lobe, hippocampus, parahippocampal gyrus, corpus callosum, cerebellum, brainstem (midbrain, pons, medulla). The variability in the size of each ROI across subjects is less than 5 mm^2^. The IVIM biexponential signal equation model is fitted using a homemade C++ implementation of the standard 2‐step algorithms based on the Levenberg‐Marquardt method. IVIM f is defined as perfusion fraction, D* is defined as pseudo‐diffusion coefficient related to microcapillary perfusion, *fD** is defined as the multiplication of *f* and *D** (related to blood flow), and D is defined as molecular diffusion coefficient. The preprocessing of NODDI data includes denoising using random matrix theory, correction for head motion and eddy current distortion, Gibbs‐ringing artifact removal, and Rician debiasing. NODDI biophysical modeling method divides water diffusion in the brain into three microstructural compartments: intracellular space through the Neurite Density Index, Orientation Dispersion Index, and Isotropic Volume Fraction. Diffusion tensors are fitted for both the multi‐shell and extracted *b* = 1000 data using a non‐linear least‐squares fitting algorithm implemented in dipy (Garyfallidis et al. 2014), from which fractional anisotropy and mean diffusivity images are generated. The NODDI model is fit by the Accelerated Microstructure Imaging via Convex Optimization implementation in Python (Daducci et al. 2015). Multiple comparisons are corrected using False Discovery Rate.

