### Randomization

2.5

As soon as informed consent is provided, the investigator should acquire the result of randomization. Stratified randomization, employing two strata (MCS and UWS), is utilized to ensure balanced proportions of UWS and MCS patients in each group. A secure randomization software is used to perform the randomization (computerized random numbers). Patients will be randomized in a 1:1 ratio to receive EA or sham‐EA treatment.

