## Discussion

3

DOC is a common consequence of TBI, but the clinical management of DOC remains a great challenge despite many efforts devoted to this long‐standing problem (Thibaut et al. 2019). Many ancient records and modern studies have shown that acupuncture may have a beneficial effect on DOC due to TBI (Cavalli et al. 2018). The AcuDoc trial is the first randomized and sham‐controlled trial to investigate the therapeutic effects and mechanisms of EA in TBI‐induced DOC through a multimodal approach.

Previous randomized trials of non‐pharmacological interventions for DOC have sample sizes ranging from 10 to 30^3^ (Barra et al. 2022; Spaccavento et al. 2024; Bai et al. 2017; Angelakis et al. 2014). In this trial, we plan to enroll 50 patients, and this sample size can detect a clinically important difference of 1.3 in the total score change of CRS‐R between the two groups. Moreover, previous trials usually include DOC patients with all kinds of etiologies (Hu et al. 2024), such as stroke, hypoxic‐ischemic encephalopathy, and TBI. However, outcomes vary widely by etiology, which will bias the assessment of treatment efficacy. This trial only included patients with DOC due to TBI within 3 months and used stratified randomization to ensure balanced proportions of UWS and MCS in the two groups to minimize biases. Blinding is a challenging yet crucial procedure in conducting randomized trials of non‐pharmacological therapies for DOC (Martens et al. 2020). However, very few non‐pharmacological DOC studies have employed a sham control, and none of the previous trials investigating the effects of acupuncture or EA on DOC or coma were sham‐controlled (Chen et al. 2021; Xin et al. 2022; Matsumoto‐Miyazaki et al. 2016). Although many DOC patients are unable to perceive whether or not they are receiving acupuncture treatments, the medical care provided by physicians, nurses, or caregivers may be biased by the setting of unblinding. In this trial, we adopted a classical masking method used in previous high‐quality randomized trials of EA (Liu et al. 2017): sham acupoints, sham acupuncture, and sham conductor wire are used in the sham‐controlled group.

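### The article does not say whether the unadjusted test or the adjusted model decides the primary outcome, and neither includes the UWS/MCS stratum used for randomisation

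*Protocol article*

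**What the plan says.** Section 2.13 (Statistical and Analytical Plan) sends the primary outcome and the secondary outcomes (BCI accuracy, GOS-E) down two routes. One is unadjusted, a t-test or Mann-Whitney; the other is a model. The wording is "U test (whichever is proper) and will be analyzed by bootstrap analyses in general linear models". The model is "adjusted for age, sex, time from injury to enrollment, and baseline CRS score" and is meant to yield odds ratios with 95% intervals. The threshold is general: two-sided "p values ≤ 0.05 will be considered significant". The section gives no criterion for choosing between the two unadjusted tests and no order between the unadjusted and adjusted results.

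Section 2.5 (Randomization) stratifies by UWS and MCS, which "is utilized to ensure balanced proportions of UWS and MCS patients in each group". That stratum is not in the covariate list of section 2.13.

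Section 2.12 (Sample Size) refers only to a two-sided "significance test with a 5% type I error" and does not name the test.

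**The concern.** Two matters are open. First, the unadjusted and adjusted p values can fall on opposite sides of 0.05, which is plausible with 50 patients. The article would then not say whether the trial succeeded, and freedom to report the better result raises the false-positive rate. Second, when randomisation balances a prognostic factor and the analysis ignores it, the unadjusted standard error is too large. The test then rejects too seldom, and part of the benefit of stratifying is lost.

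The model as described cannot settle the first matter. A general linear model of a change score gives a mean difference, not an odds ratio, so the effect measure for the primary outcome is also unclear.

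**Working it through.** **Inputs.** The difference is 1.3 points (section 3: "clinically important difference of 1.3 in the total score change of"). The SD of change is 1.6, given for the sham arm (section 2.12: "score of 0 (±1.6), and that EA treatment would result in a" 1.3-point gain) and used here for both arms. Alpha is 0.05 two-sided, loss is 4%, allocation is 1:1. Power is not stated; 80% is assumed. The stratum difference in mean change, g, is not in the documents, so it is varied over 0, 1 and 2 points.

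**The plan's own figure.** n per arm = 2(1.960 + 0.842)² × 1.6² / 1.3² = 2 × 7.85 × 2.56 / 1.69 = 23.8, so 24. Then 24 / 0.96 = 25 per arm, 50 in total. The stated figures reproduce at 80% power. (The source trial's active arm, "while the total change after tDCS treatment was 1 (±2.6"), had a larger SD; that is a separate question on which this point does not rest.)

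**Effect of omitting the stratum, by formula.** With equal strata balanced between arms and total SD held at 1.6, the between-stratum variance is g²/4 and the within-stratum variance is 2.56 - g²/4. The t-test uses the former SD of 1.6, while the treatment difference varies only with the within-stratum SD. The effective critical value is therefore 2.013 × 1.6 / √(2.56 - g²/4).

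- g = 1: √2.31 = 1.520; 2.013 × 1.6 / 1.520 = 2.119; two-sided normal tail about 3.4%.
- g = 2: √1.56 = 1.249; 2.013 × 1.6 / 1.249 = 2.579; two-sided normal tail about 1.0%.

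The unadjusted test is thus conservative, not liberal.

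**Simulation.** 24 per arm, total SD 1.6, integer scores, equal strata exactly balanced between arms, normal or skewed errors, time from injury prognostic (correlation 0.4) or not. There were 6,000 null and 3,000 alternative runs per scenario, and ordinary least squares stood in for the bootstrap model. Ranges are over the four scenarios at each g.

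| | g = 0 | g = 1 | g = 2 |
|---|---|---|---|
| Type I error, t-test | 4.5-5.2% | 3.5-3.8% | 1.1-1.5% |
| Type I error, better of t-test and Mann-Whitney | 5.8-6.3% | 4.4-4.6% | 1.2-1.6% |
| Type I error, most favourable of all three | 7.0-8.1% | 6.2-7.3% | 4.7-4.9% |
| Power, t-test | 76-79% | 77-79% | 80-83% |
| Power, treatment + stratum | 76-79% | 80-82% | 90-93% |
| Change in power from adding the stratum to the planned model | -0.8 to -0.4 | +0.3 to +1.1 | +3.5 to +5.2 |

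Monte Carlo standard error is √(0.05 × 0.95 / 6000) = 0.3 points for the error rates and √(0.8 × 0.2 / 3000) = 0.7 points for a single power.

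A second simulation at the same total SD gave type I errors for the unadjusted test of about 4.5%, 4% and 1.3% at g = 0, 1 and 2. Its most favourable result gave about 6% at 0-1 points and 4% at 2. Over the simulations, the gain from the stratum against the t-test is about 0-3 points at g = 1 and about 8-11 at g = 2.

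A single pre-specified test that includes the stratum holds 4.5-5.5% in every scenario.

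**The case against.** The strongest reply is that the article plans one unadjusted test, chosen from two, and a model whose stated purpose is estimation. Nowhere does it permit success on any favourable result. The sample size rests on a comparison of mean changes without covariates, so the natural reading is that the unadjusted test decides. A condensed article may also leave the order of analyses to a statistical analysis plan. Much of this stands. The best-of-three figure is an upper case, and choosing between t-test and Mann-Whitney by a normality check gives 4.6-5.4% with no stratum effect, which is no material inflation. What does not fall away is that the article itself fixes the tests, the covariate list and a common threshold. A later plan that named one model with the stratum would have to depart from it.

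It is also fair that UWS/MCS is diagnosed from the CRS-R (section 2.9), so baseline CRS-R already carries much of the stratum's information into the planned model.

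A reader might go further, in three ways the documents do not support:

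- That omitting the stratum inflates false positives. The formula and the simulations show the reverse.
- That inflation and marked power loss occur together. Inflation appears when the stratum is weakly prognostic, where adding it gains little; the large power loss appears when it is strongly prognostic, where there is no inflation.
- That this point shows the trial to be underpowered. Power well below 80% for the t-test arises here only if 1.6 is treated as the residual SD with stratum variation added on top, whereas section 2.12 gives it as the SD of the total change.

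The independent-test figure, 1 - 0.95³ = 14.3%, does not apply either, because the three results come from the same data and are strongly correlated.

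**Conclusion.** The point holds as a defect of specification with modest consequences. No deciding analysis is named for the primary outcome, and the randomisation stratum is in none of the analyses.

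Free choice of result would give about 6-8% false positives for a stratum difference of 0-1 points, and none in excess at 2 points. Leaving the stratum out costs the unadjusted test at most about 3 points of power at a 1-point difference and about 10 at 2 points. For the planned model the change is between about -1 and +5 points.

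These figures rest on an assumed range for the stratum difference, a total SD of 1.6 in both arms, and exact balance of strata between arms. Section 2.5 describes no blocking, and with looser balance the conservatism shrinks. The other covariates were given little or moderate prognostic weight; stronger covariates would pull the adjusted and unadjusted results further apart. This is a worthwhile, nearly free improvement, and not a flaw that invalidates the design.

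**What to change.** In section 2.13, name one primary analysis: a linear model of CRS-R change on treatment, baseline CRS-R, UWS/MCS stratum, age, sex and time from injury. Report the adjusted mean difference with a bootstrap 95% interval, not an odds ratio. State that the t-test or Mann-Whitney is a sensitivity analysis that cannot declare success. Add the stratum to the secondary-outcome models. Fix this before unblinding.

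The cost is wording and one degree of freedom. No new data are needed and the total stays at 50. Against the planned model, adding a stratum that turns out not to be prognostic loses under 1 point of power.

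Two trade-offs belong to choosing the full model at all. If none of its covariates is prognostic, it has about 4 points less power than the plain t-test (74.5% against 78.7% in the normal-error runs). With strongly skewed (exponential) errors and no stratum effect, the Mann-Whitney test had more power than the full model (87-93% against 72-80%). A sponsor who expects such skew could name a stratified rank test as primary instead. The essential step is that one test is named in advance and uses the stratum.
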